### 2.9. Sample Size Assumptions and Justification

For the sample size calculation, a non-inferiority design is assumed and the upper limit of the 95% confidence interval (CI) of the difference of proportions in grade 3 or higher adverse events at 8 percentage points has been set. We assume that 5% of patients will not be assessable. Alpha risk is set in 0.1 and power in 0.8. Based on the previous literature and our previous experience, expected standard treatment grade ≥ 3 AE are 5–10% (mean 8%) among experimental arms and standard treatment arms. Considering this, the number of participants per arm has been calculated to be 134 participants. Because of the limited recruitment capacity for this trial, we could not target specific numbers of participants for each sub-group of risk factors. 

Based on a feasibility survey performed at the planning stage, the target enrollment rates per country were: Paraguay 6.25 participants per month; Spain, Portugal, and the Netherlands 1.6 participants per month.

### 2.10. Main Outcomes Analysis

The primary safety outcome will be analyzed as the proportion of participants in the HR^35^ZE and historical HR^10^ZE groups that received at least one dose of treatment with an unfavorable outcome after 8 weeks of experimental treatment start. According to the clinical and laboratory information, participants will be classified as having an unfavorable outcome if they suffered one or more grade ≥ 3 AE or SAE that are possibly, probably, or definitely related to rifampicin OR they did not complete their treatment because of other reasons OR were lost-to follow-up. High doses of rifampicin will be considered non-inferior to standard doses if the upper boundary of the 95% CI of the proportion of participants with an unfavorable outcome is less than 8% that of the point estimate in the historical standard dose group.

Efficacy will be assessed as the proportion of participants with pulmonary TB in the HR^35^ZE and the historical HR^10^ZE groups that have sputum culture conversion in liquid media at week 8. The unfavorable efficacy outcome will be defined as having a positive sputum culture at week 8.

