### 2.2. Objectives and Endpoints

The study primary objective is to evaluate the safety of high-dose rifampicin (35 mg/kg/d) as part of a standard first line regimen using standard doses of isoniazid (5 mg/kg), pyrazinamide (25 mg/kg), and ethambutol (15–25 mg/kg) for 8 weeks in adult subjects with pulmonary or extrapulmonary DS-TB belonging to difficult to treat subgroups. The secondary objectives are to evaluate the tolerability, efficacy, bactericidal activity, pharmacokinetic/pharmacodynamics, and cost effectiveness of high dose rifampicin, among others. 

The primary safety endpoint is the proportion of participants and historical controls with one or more grade 3 or higher adverse events (AE) according to the CTCAE v5 or SAE at 8-weeks after treatment with high-dose rifampicin onset. Table 2 below describes in detail the analysis population and primary safety outcomes. The secondary tolerability endpoint includes the proportion of participants with any AE. The secondary efficacy endpoint includes the proportion of participants and historical controls who have sputum culture conversion at 8 weeks after treatment onset or a proportion of participants with clinical improvement according to the treating physician (if follow-up images are available for extra-pulmonary TB) but without a follow up sample at 8 weeks after treatment onset.

Most TB phase 2 trials complete their intervention at week 8 or earlier and then participant care is transferred to a public institution within the National TB programs, so the information about end of treatment and post-treatment outcomes is scarce [10,17,18]. In the RIAlta trial, after the intervention and the primary safety objective evaluation, an extended follow-up period will be offered to participants, in line with the phase 2b/c design suggested by Phillips et al. [19]. This will provide information about end-of-treatment outcomes and relapse incidence in the prospective group.

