### 2.8. Assessment of Study Outcomes, Analysis Groups, and Duration of Follow-Up

The primary safety hypothesis is that the incidence of adverse events in the high dose rifampicin (35 mg/kg) supplemented with isoniazid, pyrazinamide, and ethambutol [HR^35^ZE] during the first 8 weeks of treatment will not exceed that of controls on a standard HRZE regimen (rifampicin 10 mg/kg) [HR^10^ZE]. The HR^35^ZE regimen will be considered unsafe if in a non-inferiority analysis, the upper limit of the 95% confidence interval of the difference of proportions in grade ≥ 3 AE (according to CTCAE scale version 5) between the experimental and the historical control arm exceeds 8%. The most common adverse events related to therapy with higher rifampicin doses were vomiting, headache, hyperuricemia, pain in the extremities, and pruritus. No significant differences according to rifampicin dose (from 10 to 35 mg/kg) were found in a recent systematic review and in a retrospective study collecting the real-life experience from a Dutch center [24,25].

To assess the AE and ensure a homogeneous evaluation of their grade, severity, expectedness, and treatment relatedness, we will administer a standardized training for the investigators from all different sites. In addition, both for the prospective and the retrospective cohorts, grade 3 or higher adverse events and SAE will be reviewed by the trial’s Steering Committee for relatedness classification. When no consensus is reached, the Data and Safety Monitoring Board formed by experts independent from the trial will make the final decision.

Tolerability will be measured as any adverse event (grade 1 to 4), treatment dropout rate, and any dose reduction. For efficacy outcome, the hypothesis is that in DS-TB participants (pulmonary disease), the proportion of participants experiencing successful treatment outcomes (culture and smear negative) at the end of the intensive phase of treatment on HR^35^ZE will be non-inferior to that of controls on HR^10^ZE. The HR^35^ZE regimen will be considered ineffective if the lower limit of the 95% CI of the proportion of participants with a negative sputum culture (sputum sterilization), or unable to produce sputum if they have a previous negative culture at week 8, is more than 10% lower than that of historical controls treated with HR^10^ZE. Other exploratory outcomes will be reported descriptively. 

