Therefore, the population included in this study belong to the other risk factors groups for failure and relapse that have been under-represented in previous clinical trials [4,22]. As a phase 2 study, the main aim of this clinical trial is to evaluate safety of rifampicin defined as the rate of participants suffering grade 3 or higher adverse events or severely adverse events. This information will be likely available from historical controls although it was not systematically collected. Grade 1–2 adverse events, which are considered tolerability problems, are not typically reported in clinical records, or the information about them is not complete, thus making it difficult to make comparisons. To address this, we have developed adverse events monitoring and management guidelines, which will be harmonized at all centers for the prospective part. Extensive training will be provided to the investigators at each site. 

It is important to acknowledge the main limitations related to this trial design. Because of the limited recruitment capacity within our consortium and budgetary constraints, we decided to use historical controls (rifampicin 10 mg/kg along with the same TB regimen) and assign all prospectively recruited participants to the 35 mg/kg dose. This results in a non-randomized design as all participants will be assigned to the experimental arm and compared with historical controls. Hence, another limitation is that information about tolerability is often incomplete or not reported in clinical records, and the endpoints in the different sub-studies are not performed in daily clinical practice. For similar reasons, the sample size is too small for a formal subgroup analysis. The results will inform a larger phase 3 trial with power calculations for relevant subgroups.

Having one PK sampling at week 4 will allow us to show the percentage of participants reaching the target exposure (AUC/MIC) when in a steady state after rifampicin induction of its own metabolism. In contrast, this approach will not provide information about exposure during the first week of treatment, when most of the bacterial killing occurs. Nevertheless, this knowledge will aid our understanding if optimized rifampicin dosing is more likely to meet target rifampicin exposure. 

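### The primary safety endpoint has incompatible definitions, and the 8% rate, 8-point margin and 134 per arm do not apply to the section 2.10 composite

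*Protocol article*

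**What the plan says.** Section 2.2 words the primary safety endpoint, assessed at week 8, as follows: "proportion of participants and historical controls with one or more grade 3 or higher adverse events (AE) according to the CTCAE v5 or SAE". The Abstract agrees, and the Discussion speaks of "safety of rifampicin defined as the rate of participants suffering grade 3 or higher adverse events or severely adverse events". None of these mentions relatedness, non-completion or loss to follow-up.

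The decision rule in section 2.8 applies an upper 95% confidence limit to this quantity: "difference of proportions in grade ≥ 3 AE (according to CTCAE scale version 5) between the experimental and the historical control arm exceeds 8" per cent. Section 2.9 plans on the same quantity: "expected standard treatment grade ≥ 3 AE are 5–10% (mean 8%) among experimental arms and standard treatment arms". It adds: "We assume that 5% of patients will not be assessable".

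Section 2.10, which describes the primary analysis, classifies a person as unfavourable if they had grade 3 or higher adverse events or SAEs "possibly, probably, or definitely related to rifampicin OR they did not complete their treatment because of other reasons OR were lost-to follow-up". Section 2.8 provides for the relatedness judgement in both cohorts, through review by the "Steering Committee for relatedness classification", with an independent board deciding where there is no consensus. The same section places treatment dropout under tolerability, which is a secondary matter.

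Section 2.2 refers the reader to Table 2 for the primary safety outcomes, but Table 2 lists analysis populations only.

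**The concern.** The definitions classify the same patient differently. Someone who has an SAE judged unrelated to rifampicin and completes treatment and follow-up is an event under section 2.2 and a non-event under section 2.10. Someone lost at week 5 without toxicity is the reverse. Two analysts working from two sections would report different primary results. In an open-label study with historical controls, that leaves room to settle the definition after the data are known.

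The second stake is what the margin means. Eight percentage points of excess adverse events is a statement about toxicity. Eight points on a mixture of related toxicity, non-completion and loss is not. Non-completion and loss are not safety events, and their frequency may differ between patients followed in a trial and patients reconstructed from routine records. A difference between cohorts in those components moves the primary comparison without any difference in toxicity.

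**Working it through.** **1. Definitions side by side**

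| Place | Grade ≥3 AE | SAE | Must be rifampicin-related? | Non-completion or loss an event? |
|---|---|---|---|---|
| Abstract, 2.2, Discussion | yes | yes | not stated | no |
| 2.8 rule, 2.9 sample size | yes | not mentioned | not stated | no |
| 2.10 | only if related | only if related | yes | yes |

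**2. The plan's own figure**

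Inputs from section 2.9: margin 0.08, alpha 0.1, power 0.8, rate 5–10% (mean 8%), 5% not assessable.

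n per arm = 2p(1−p)(z₁₋α + z₀.₈)² / 0.08², then divide by 0.95.

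- p = 8%, one-sided 0.10: 0.1472 × (1.2816 + 0.8416)² / 0.0064 = 103.7, so 104, then 110.
- p = 10%, one-sided 0.10: 0.18 × 4.508 / 0.0064 = 126.8, so 127, then 134.
- p = 8%, one-sided 0.10 with continuity correction: 128, then 135.

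So 134 can be reached as a calculation on grade 3 or higher adverse events, using the top of the stated range (10%) in both arms. The article does not say which variant was used.

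**3. What the composite does to the rate**

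With adverse-event rate a, loss or non-completion rate l, and independence assumed, composite = 1 − (1−a)(1−l).

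- a = 8%, l = 5%: 1 − 0.92 × 0.95 = 12.6%.
- If only half of the 8% were judged related (an assumption), with l = 5%: 1 − 0.96 × 0.95 = 8.8%.

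Loss raises the rate and the relatedness filter lowers it. The article gives no figure for either, so the net rate is unknown.

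**4. Power when the arms truly do not differ**

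Power = Φ(0.08/SE − z), SE = √(2p(1−p)/134). The adverse-event rate is 8% in both arms, l is equal in both (assumed) and the relatedness filter is ignored.

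| l | Composite | 95% CI rule (z = 1.96) | One-sided 0.10 (z = 1.2816) |
|---|---|---|---|
| 0 | 8.0% | 67.5% | 87.1% |
| 5% | 12.6% | 50.5% | 75.5% |
| 10% | 17.2% | 41.1% | 67.5% |
| 20% | 26.4% | 31.8% | 58.1% |

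The 67.5% in the first row already reflects a separate matter: the size was set with alpha 0.1 while the decision uses a 95% interval. Only the fall down each column belongs to this point.

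**5. Bias when toxicity truly differs**

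True adverse-event rates are 16% (35 mg/kg) and 8% (control), exactly at the margin, with 134 per arm, the 95% CI rule and the relatedness filter ignored. P(NI) = Φ((0.08 − d)/SE − 1.96), where d is the difference in composite rates and SE is unpooled. Loss rates by cohort are assumptions.

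| Loss, prospective / historical | Composite, prospective / historical | d (points) | P(declare NI) |
|---|---|---|---|
| 0 / 0 | 16.0% / 8.0% | 8.0 | 2.5% |
| 10% / 10% | 24.4% / 17.2% | 7.2 | 3.6% |
| 5% / 10% | 20.2% / 17.2% | 3.0 | 18.2% |
| 3% / 10% | 18.5% / 17.2% | 1.3 | 29.7% |
| 10% / 3% | 24.4% / 10.8% | 13.6 | about 0.1% |

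Example, row four: 1 − 0.84 × 0.97 = 0.1852; 1 − 0.92 × 0.90 = 0.172; SE = √((0.1852 × 0.8148 + 0.172 × 0.828)/134) = 0.0468; (0.08 − 0.0132)/0.0468 − 1.96 = −0.53; Φ = 0.297.

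**The case against.** Counting losses as unfavourable is a defensible convention, and a protocol may choose it. The direction of any bias is also not known. Trial follow-up may lower loss in the prospective arm, but that arm takes additional rifampicin tablets, so non-completion could be higher there, and the composite would then be conservative. A reader might infer that the composite hides a toxicity excess; the documents give no loss rates and do not support that direction over the other. Equal loss has a small effect: it shrinks the difference by the factor (1 − l) as well as adding variance.

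A reader might also infer that section 2.10 pushes the event rate above 8%, or that 134 is wrong. Neither is shown. The relatedness filter could offset the loss component, and 134 is reproducible for adverse events. What stands is that 8% was stated for a different quantity.

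It is tempting to say that section 2.9 removes as not assessable the very people section 2.10 counts as events. Section 2.9 does not define the term, and it could mean exclusions of the kind Table 2 lists, such as non-tuberculous mycobacteria or early withdrawal of consent. It is likewise tempting to fault the relatedness review as unblinded or as left to the trial's own committee. Section 2.8 has an independent board for unresolved cases, and a condensed article may omit blinding details.

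Finally, sections 2.2, 2.8 and 2.9 are silent on causality rather than explicit that cause is disregarded. The Discussion also concedes that control adverse-event data were not systematically collected, so an endpoint without the filter has its own ascertainment problem. Both points are fair. Neither reconciles section 2.10 with the other sections.

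**Conclusion.** The contradiction stands on the text alone and needs no assumption. The section that governs the analysis tests a different quantity from the one the hypothesis, margin and sample size were written for, and it moves dropout from tolerability into primary safety. This should be fixed before any analysis.

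The numerical consequences are illustrative. They rest on assumed loss rates, on independence of loss and adverse events, on 1:1 matching at 134 per arm, and on leaving out the relatedness filter. Within those limits, differential loss of a few points can move the chance of accepting a regimen at the margin from 2.5% to anywhere between about 0.1% and 30%. A 5% loss component in both arms costs 17 points of power under the 95% CI rule (67.5 − 50.5), or about 12 at one-sided 0.10 (87.1 − 75.5).

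**What to change.** State one primary safety endpoint in the Abstract and in sections 2.2, 2.8, 2.9 and 2.10: grade 3 or higher adverse event or SAE by week 8, among all who received at least one dose, regardless of relatedness. This is the definition closest to the one the margin and sample size were built on. Confirm at the same time that the 5–10% planning range covers SAEs below grade 3, since sections 2.8 and 2.9 name adverse events only.

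Report non-completion and loss to follow-up separately by cohort. Prespecify the same handling of incomplete safety follow-up in both cohorts, and keep the section 2.10 composite as a sensitivity analysis. Keep rifampicin-relatedness as a secondary classification.

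If the composite is to remain primary, state its expected rate in each cohort, justify a margin for it, and recompute the power.

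The recommended route costs wording changes and a short prespecified missing-data rule, with no added patients. Keeping the composite could require a larger sample, depending on the rate assumed.

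### Section 2.10 tests the HR35ZE upper limit against the control point estimate, while sections 2.8 and 2.9 use the interval for the difference, so the same counts can pass one rule and fail the other

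*Protocol article*

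**What the plan says.** Section 2.8 says that the higher-dose "regimen will be considered unsafe if in a non-inferiority analysis" a stated limit is above 8%. The limit it names is "the upper limit of the 95% confidence interval of the difference of proportions in grade ≥ 3 AE", taken across the two arms. The statistic is a difference and the interval belongs to that difference.

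Section 2.9 sizes the trial on the same quantity, "the upper limit of the 95% confidence interval (CI) of the difference of proportions in grade 3 or higher adverse events at 8 percentage points". It adds "Alpha risk is set in 0.1 and power in 0.8", 5% not assessable, and an expected rate of grade 3 or higher events of 5-10% (mean 8%) in both arms, and arrives at 134 per arm.

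Section 2.10, the main outcomes analysis, has the high-dose regimen "considered non-inferior to standard doses if the upper boundary of the 95% CI of the proportion of participants" affected is low enough. Its threshold is worded as follows: "the proportion of participants with an unfavorable outcome is less than 8% that of the point estimate in the historical standard dose group". Here the interval belongs to one proportion and the comparator is a point estimate. The sentence does not name HR35ZE, but a comparison with the historical group's estimate leaves no other arm.

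The article does not say which statement governs.

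**The concern.** A rule that sets a one-arm confidence limit against the control estimate treats the historical rate as known. That rate comes from a chart-review cohort that may be no larger than the treated one, and the Discussion (section 3) concedes that these events were not systematically collected in it. Leaving out the control variance shortens the interval, so the rule is easier to pass than the one in 2.8 and 2.9.

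The rule yields the trial's main conclusion, on the safety of a higher dose in vulnerable patients. If both statements stand, some plausible results would be non-inferior under 2.10 and unsafe under 2.8. The phrase about 8% of the control estimate adds a second uncertainty, because it can be read as a relative margin.

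**Working it through.** **Inputs.** Margin of 8 points and 95% intervals (2.8, 2.9, 2.10); 134 per arm, 5% not assessable, rates of 5-10% with mean 8% (2.9); controls at least 1:1 (Abstract). Assessable per arm: 134 × 0.95 = 127.3, taken as 127. Assumptions: the same endpoint is counted under both rules, matching is ignored, and 8% is absolute.

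**The plan's own figure.** n = (z_alpha + z_beta)² × 2p(1−p) / 0.08². With p = 0.10, one-sided alpha 0.10 and power 0.80: (1.2816 + 0.8416)² × 0.18 / 0.0064 = 126.8, so 127; 127/0.95 = 133.7, so 134. The stated figure reproduces, and it is a calculation for a difference between two arms. At the stated mean of 8% none of the usual alphas gives 134: 110 (one-sided 0.10), 151 (0.05), 191 (0.025).

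**The two rules** (T = HR35ZE, C = control):
- 2.8/2.9, Wald: pT − pC + 1.96·√[pT(1−pT)/nT + pC(1−pC)/nC] < 0.08. Newcombe: pT − pC + √[(uT − pT)² + (pC − lC)²] < 0.08, with u and l the Wilson limits.
- 2.10: uT − pC < 0.08, with uT the Wald or Wilson upper limit.

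The 2.10 quantity is the 2.8 quantity with the control term removed from under the root. It can never be the larger of the two, so every disagreement runs one way: 2.10 passes and 2.8 fails.

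**Worked example, 12/127 v 10/127.** pT = 0.0945, pC = 0.0787, difference 0.0157. Standard errors: T 0.02596, C 0.02390, difference 0.03528. The control share of the variance is 0.02390²/0.03528² = 46%.
- 2.8, Wald: 0.0157 + 1.96 × 0.03528 = 0.0849, or 8.5 points. Newcombe: 0.0157 + √(0.0634² + 0.0354²) = 0.0884, or 8.8 points. Unsafe.
- 2.10, Wald: 0.0157 + 1.96 × 0.02596 = 0.0666, or 6.7 points. Wilson: 0.1579 − 0.0787 = 0.0792, or 7.9 points. Non-inferior.

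A Clopper-Pearson limit gives 8.05 points here and would just fail. With 134 per arm, 13 v 11 events conflict under all three: 8.3 (Wald) or 8.6 (Newcombe) for the difference, against 6.5 (Wald), 7.7 (Wilson) or 7.8 (Clopper-Pearson).

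**How often.** All pairs of binomial counts were enumerated. Each cell gives Wald, then Wilson/Newcombe.

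| Assessable, true rates (T v C) | Pass under 2.8/2.9 | Pass under 2.10 | Rules disagree |
|---|---|---|---|
| 127 v 127, 8% v 8% | 66% / 62% | 80% / 70% | 14% / 8% |
| 127 v 127, 16% v 8% | 2.9% / 2.5% | 8.0% / 4.7% | 5.1% / 2.1% |
| 127 v 254, 8% v 8% | 76% / 67% | 83% / 73% | 6.7% / 5.8% |
| 127 v 254, 16% v 8% | 3.6% / 2.3% | 6.2% / 3.3% | 2.6% / 1.1% |

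Rows at 16% v 8% put the true excess exactly at the margin, so a pass there is a false declaration of non-inferiority.

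**The case against.** The best defence is that 2.10 is loosely drafted and not a second rule. Section 2.8 words the efficacy criterion in a similar way, as the limit of a proportion compared with the historical controls, and 2.8 and 2.9 state the safety criterion plainly. That may well explain the origin of the sentence. It does not remove the conflict, because the section headed as the main analysis still gives a different statistic and no order of precedence.

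Four stronger readings are tempting, and the documents do not support them.

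- **A relative 8% margin.** On that reading (limit below 1.08 times the control rate), an equally safe regimen would pass only 9-16% of the time. Section 2.9 fixes the margin in percentage points, so this shows that the wording is poor, not that such a rule was intended.
- **A breach of the declared error rate.** The 2.5% benchmark comes from the 95% interval. Section 2.9 also sets alpha at 0.1, and 8.0% lies within that. What stands is that 2.10 is more lenient than 2.8 and that the article's own error levels do not agree.
- **A large conflict across any plausible table.** It depends on the interval method and the control ratio. At 13/127 v 10/127, for example, the conflict appears with Wald (9.4 v 7.6 points) but not with Wilson (8.9 points, a fail under both). Section 2.5 aims to include all eligible 2017-2019 patients, so 1:1 is the minimum and the disagreement shrinks with more controls.
- **Opposite verdicts on literally the same data.** Section 2.8 counts grade 3 or higher events. Section 2.10 counts rifampicin-related grade 3 or higher or serious events, plus non-completion and loss to follow-up. The conflict above is shown on one common endpoint; the difference in endpoints is a further inconsistency.

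**Conclusion.** The concern holds. The article gives two primary decision rules that are not equivalent. The 2.10 version omits the control variance, and any disagreement favours HR35ZE. At 1:1 with 127 assessable per arm, the rules part in 14% (Wald) or 8% (Wilson/Newcombe) of trials when both true rates are 8%. When the excess equals the margin, false non-inferiority rises from 2.9% to 8.0% (Wald) or from 2.5% to 4.7% (Newcombe to Wilson). With twice as many controls the disagreement is about 6-7%. These sizes assume independent binomial counts, a common endpoint, an absolute margin and rates taken from section 2.9 for grade 3 or higher events; the article gives no expected rate for the wider composite in 2.10.

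A reader might infer that the sponsor means to choose between verdicts. Nothing in the article suggests that. The point is that the rule must be settled before the counts are known.

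**What to change.** Replace the decision sentence in 2.10 with the rule of 2.8 and 2.9: HR35ZE is non-inferior if the upper limit of the two-sided 95% confidence interval for HR35ZE minus HR10ZE is below 8 percentage points, absolute. Name the interval method, and state that it includes the sampling variance of both cohorts. Use one definition of the primary endpoint in 2.8, 2.9 and 2.10.

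In 2.9, reconcile the alpha of 0.1 with the 95% interval and restate the power. At 8% v 8% with 127 assessable per arm it is about 62% (Newcombe) to 66% (Wald), not 80%.

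The cost is a few sentences and a less favourable stated power, with no extra patients. Keeping the 80% claim with a 95% interval would be a separate decision and not free: by the formula above with one-sided 0.025, about 181 assessable per arm (181/0.95 = 191 enrolled) at 8%, or 221 (233) at 10%.

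### Section 2.10 sets the confidence limit of one proportion against the historical point estimate, contradicting the interval for the difference in 2.8 and 2.9 and, read literally, roughly doubling the false non-inferiority rate

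*Protocol article*

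**What the plan says.** The protocol article states the primary safety rule three times.

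- **Section 2.8** calls the regimen unsafe if the "upper limit of the 95% confidence interval of the difference of proportions in grade ≥ 3 AE" between the experimental and historical arms exceeds 8%.
- **Section 2.9** sizes the trial on the same quantity, the "upper limit of the 95% confidence interval (CI) of the difference of proportions in grade 3 or higher adverse events at 8 percentage points". It adds "Alpha risk is set in 0.1 and power in 0.8" and assumes that "expected standard treatment grade ≥ 3 AE are 5–10% (mean 8%) among experimental arms and standard treatment arms".
- **Section 2.10**, which describes the main analysis, declares non-inferiority when the upper 95% limit for the "proportion of participants with an unfavorable outcome is less than 8% that of the point estimate in the historical standard dose group". No interval for a difference appears.

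The efficacy rule in 2.8 has the same single-proportion form. It takes the "lower limit of the 95% CI of the proportion of participants with a negative sputum culture" and asks whether it is more than 10% below the result in historical controls.

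The abstract promises at least one matched control per participant. Section 2.5 describes the controls as patients treated at the participating sites from 2017 to 2019. They are a sample, not a fixed reference rate.

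**The concern.** A limit computed from the HR35ZE group alone carries only that group's sampling error. Setting it against the historical point estimate plus 8 points treats the estimate as if it were the true control rate. The resulting limit is too close to the observed difference, so non-inferiority is declared too easily.

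This rule decides whether the higher dose is called acceptably safe in patients chosen for their vulnerability, and the error runs towards calling it safe. With two rules in print, the conclusion could depend on which section the analyst follows, and a choice made after the data are seen could not be excluded.

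**Working it through.** **Inputs.** From 2.9: 134 per arm, 5% not assessable, margin 8 percentage points, expected rate 5–10% (mean 8%) in both arms, alpha 0.1, power 0.8. The interval method is not stated, so several were tried. Independent arms and exactly 1:1 controls are assumed unless noted. One endpoint is used for both rules.

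**1. The plan's own figure.** For equal true rates p, n = (z₁₋α + z₀.₈)² × 2p(1−p) / 0.08².

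- p = 10%, one-sided alpha 0.10: (1.282 + 0.842)² × 0.18 / 0.0064 = 126.8, so 127. Then 127 / 0.95 = 133.7, so **134**. This reproduces the plan.
- p = 8%, one-sided 0.10: 104, or 110 after the 5% loss.
- p = 8%, one-sided 0.025 (which a 95% CI implies): 181, or 191 after loss.

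So 134 is reproduced as a two-sample difference calculation, at the top of the stated rate range and with a looser alpha than a 95% CI carries.

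**2. The two rules.** With observed proportions pE and pC:

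- Section 2.10, read literally: upper 95% limit of pE < pC + 0.08.
- Sections 2.8 and 2.9: upper 95% limit of (pE − pC) < 0.08.

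**3. False non-inferiority at the margin (true rates 8% and 16%).** Normal approximation for the 2.10 rule: Φ(−1.96 × SE_E / SE_diff).

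- Var_E = 0.16 × 0.84 / 134 = 0.001003, so SE_E = 0.0317.
- Var_C = 0.08 × 0.92 / 134 = 0.000549, so SE_diff = √0.001552 = 0.0394.
- Φ(−1.96 × 0.0317 / 0.0394) = Φ(−1.576) = **5.8%**, against 2.5%.
- Control share of the variance: 0.000549 / 0.001552 = 35%.

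Exact enumeration of the two binomials:

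| Controls per participant | 2.10, Wilson | 2.10, Wald | Difference, Newcombe | Difference, Wald |
|---|---|---|---|---|
| 1:1 | 4.7% | 7.8% | 2.6% | 2.9% |
| 2:1 | 3.3% | 6.2% | 2.2% | 3.5% |
| 3:1 | 2.9% | 5.6% | 2.1% | 3.8% |

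Like for like at 1:1, the ratio is 4.74 / 2.59 = 1.8 (Wilson against Newcombe) and 7.76 / 2.92 = 2.7 (Wald against Wald). With 127 assessable per arm the 2.10 figures are 4.7% and 8.0%, so the result does not hang on the exact n.

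**4. Disagreement when both arms are truly at 8% (134 per arm).**

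- Wald: 82.6% non-inferior under 2.10, 67.8% under the difference rule, a gap of 14.8 points.
- Wilson / Newcombe: 72.8% and 64.8%, a gap of 8.0 points.

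The rules are nested: every trial that passes the difference rule also passes 2.10. Each gap is therefore the share of trials given opposite verdicts.

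**5. One data set.** 13/134 (9.7%) on HR35ZE and 11/134 (8.2%) in controls.

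- 2.10: upper limit 14.7% (Wald) or 15.9% (Wilson), below 8.2% + 8 = 16.2%. Non-inferior.
- 2.8: upper limit of the difference 8.3% (Wald) or 8.6% (Newcombe), above 8%. Unsafe.

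**The case against.** The strongest reply is that the intended rule can be recovered. Sections 2.8 and 2.9, including the basis for the sample size, both specify the difference, and the sentence in 2.10 is garbled enough to look like a drafting slip. A reader might infer that a one-sample test was deliberately chosen; the article does not support that. It does state two rules, though, and the odd one stands in the main-analysis section and names the point estimate as comparator. The inconsistency remains whatever was intended.

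A reader might also say that the error rate triples. That holds at the planned rates only for a Wald limit, exactly 1:1 controls and comparison with the nominal 2.5% (7.8 / 2.5 = 3.1). No interval method is named, the Wald difference rule itself runs at 2.9%, and the article allows more than one control per participant. Roughly doubling is the supported statement. Nor is half the variance ignored at the margin: the share is 35%, and it is half only when the two rates are equal.

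The 2.10 wording could be read as a relative margin, with the upper limit below 1.08 times the control rate. Power would then be only about 9% (Wilson) or 16% (Wald). Section 2.9 says percentage points, so this reading is not supported, but the sentence should not permit it.

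Finally, 2.9 sets alpha at 0.1, and 7.8% does not exceed a one-sided 0.10. This has force against 2.5% as the only benchmark. All three statements nonetheless specify a 95% interval, and the two rules conflict at any alpha.

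**Conclusion.** The point holds as a contradiction in the primary decision rule. The 2.10 version is statistically wrong if followed as written, because it omits the sampling error of the historical controls. The sizes in the working rest on independent arms, 1:1 controls, rates near those in 2.9 and an interval method that the article does not name. Correlation induced by matching would change them.

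They also hold the endpoint fixed. Section 2.10 counts non-completion and loss to follow-up as unfavorable while 2.8 refers to grade 3 or higher events, so the disagreement rate is illustrative rather than a forecast for this trial. That endpoint difference is a separate matter.

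**What to change.** Replace the decision sentence in 2.10 with:

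> HR35ZE is non-inferior if the upper limit of the two-sided 95% CI for the risk difference (HR35ZE minus HR10ZE) is below +8 percentage points.

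Name one interval method, for example Newcombe or a covariate-adjusted risk difference. Rewrite the efficacy rule in 2.8 in the same form: the lower limit of the CI for the difference in culture conversion must lie above −10 percentage points.

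The wording change is two sentences and needs no new data. The real cost is in the power claim. At 8% in both arms, SE_diff = √(2 × 0.08 × 0.92 / 134) = 0.0331, and power = Φ(0.08 / 0.0331 − 1.96) = 67%; exact values are 65% (Newcombe) and 68% (Wald), not the stated 80%. By the sample-size formula above, 80% needs 181 assessable per arm, or 191 with 5% loss, at 1:1. The alpha of 0.1 in 2.9 does not match a 95% interval, so 2.9 and the abstract should restate power for the interval actually used.
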